**Result:**

After the primary EEG analysis using MATLAB, the amplitude, frequency, frequency band ratio, and power spectrum density will be analysed. Mixed design analysis and intention-to-treat analysis will be used to assess the efficacy of aerobic training.

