## Methodology

This study is a pilot randomized control trial with a pre-and post-test design that focuses on the preliminary efficacy of aerobic training among university students with migraine symptoms. The primary endpoint is resting-state electroencephalography (EEG). The secondary endpoints are sleep quality, quality of life, and migraine pain level. This study will be conducted at Physiotherapy Center, Universiti Tunku Abdul Rahman, Sungai Long Campus. The outcome measures will be performed at baseline and end of intervention (6^th^ week) to compare the data obtained. The study is approved by UTAR Scientific and Ethical Review Committee (U/SERC/188/2022). The informed consent form will be signed and dated before the start of the actual intervention. Parallel assignment intervention model will be used. The study is also registered with ClinicalTrials.gov Protocol Registration and Results System (Identifier: NCT05741775).

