Recording of resting-state EEG will be performed using MUSE 2 a portable EEG recording device. The headset has four dry sensors (two mastoid and two forehead sensors). It fits over the ears and extends at an angle over the middle of the forehead when properly fitted with 3 reference electrodes. Once the headband is fitted, as shown in Fig 2b, the mind monitor app will be used for data acquisition. There will be horse to represent the sensors on the Muse and its connection. Solid ovals indicate a good connection, outlines indicate a poor connection and an empty space indicates no connection. The data acquisition space will be 100–200 cm from the computer/ tablet monitor displaying the stimulus presentation sequence. In the mind monitor application, the presentation of brain wave sequence can be in absolute, raw, discrete, accelerometer, and spectrogram views. In this study, raw EEG presentation values will be used for stimulus presentation sequence. So, each sensor’s raw data will be recorded in microvolts (μV). The sensors will be TP9 (left ear), AF7 (left forehead), AF8 (right forehead), TP10 (right ear), AUXR (right auxillay). The participant will be instructed not to clench teeth and blink eyes often since it can alter the activity recorded. The resting-state EEG will be recorded for a total of 20 minutes alternating between eyes open and eyes closed condition [39–41]. Details of the SPIRIT enrollment and the experimental protocol are as illustrated in Figs 1 and 2.

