### Statistical methods

#### Analysis of EEG signals

Amplitude and frequency, frequency band ratio, power spectrum density, and coherence will be analysed for resting-state EEG recording. The recorded data from the MUSE 2 portable EEG device can be further analysed in MATLAB. The data obtained will be imported to MATLAB using EEGLAB function plugins (muse monitor app) CSV file. Once imported, the pre-processing steps will be done to run Independent Component Analysis (ICA). The sampling frequency will be set at 256Hz. To remove linear trends, high-pass filtering at 1 Hz will be done to obtain good quality Independent Component Analysis (ICA) decompositions. Average referencing for source localization will be done since a non-scalp reference is used. Artifact rejection and ICA will be used to remove artifacts such as muscle, eye blinks, or eye movements without removing the affected data portions.

After extracting epochs and plotting data, the EEG amplitude, frequency, frequency band ratio, power spectrum density, and coherence will be analysed. EEG will be decomposed into the five EEG sub-bands of frequency and amplitude: delta (0.5–3 Hz/ 5–250 microvolt), theta (4–7 Hz/ 20–100 microvolt), alpha (8–12 Hz/ 5–120 microvolt), beta (13–30 Hz/ 5–50 microvolt) and gamma (31–40 Hz/ -10 microvolt). MATLAB will design a filter with the ’butter’ command for frequency band ratio, setting the cut-off frequencies according to alpha or theta band or appropriate bands and then using it on data with the ’filter’ command.

The power spectral density of EEG will be estimated using AR Burg method. The AR method is based on modeling the data sequence x(n) as the output of a causal and discrete filter whose input is white noise, which is expressed as the follows:

$$x\left(n\right)=-\overset{p}{\underset{k=1}{\sum }}a\left(k\right)\cdot x\left(n-k\right)+\omega \left(n\right)$$

where a(k) is the AR coefficient, x(n) is the white noise of variance equal to r2, ω(n) is window function and p is the order of the AR model.

Next, the coherence estimation will be performed. Coherence represents the normalized covariance of two time series in the frequency domain. Mathematically, the coherence function C_xy_(f) at a frequency f for signal x and y is obtained by the normalization of the cross-spectral spectrum as follows:

$$C_{xy}\left(f\right)=\frac{\left|\langle P_{xy}\left(f\right)\rangle \right|}{\sqrt{P_{xx}\left(f\right)}*\sqrt{P_{yy}\left(f\right)}}$$

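### Re-referencing four EEG sensors to their own mean before estimating power and coherence creates coherence by arithmetic, can reverse a real change, and removes shared power

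*Protocol article*

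**What the plan says.** All references are to the protocol article.

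- **Endpoint** (Methodology): "The primary endpoint is resting-state electroencephalography (EEG"). No single EEG parameter is named as primary.
- **Hardware** (Outcomes): "The headset has four dry sensors (two mastoid and two forehead sensors"). The same section lists five channel names: "TP9 (left ear), AF7 (left forehead), AF8 (right forehead), TP10 (right ear), AUXR (right auxillay").
- **Parameters** (Analysis of EEG signals): "Amplitude and frequency, frequency band ratio, power spectrum density, and coherence will be analysed for resting-state EEG recording". The Result paragraph of the abstract gives a shorter list without coherence: "the amplitude, frequency, frequency band ratio, and power spectrum density will be analysed".
- **Re-referencing** (Analysis of EEG signals): "Average referencing for source localization will be done since a non-scalp reference is used".
- **Order of steps** (same section): import, 1 Hz high-pass filter, average reference, artifact rejection and ICA, epochs, then amplitude, frequency, band ratio and power spectral density. After these comes "Next, the coherence estimation will be performed".
- **Definition** (same section): "Coherence represents the normalized covariance of two time series in the frequency domain". The formula takes the magnitude of the cross-spectrum divided by the square roots of the two power spectra. The sign of the dependence is therefore lost.

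**The concern.** An average reference is meant to approximate a neutral reference when many electrodes cover the head. Here the average is taken over two forehead and two ear sites. Each re-referenced channel becomes 3/4 of itself minus 1/4 of each of the other three, and the four signals sum to zero at every instant. The off-diagonal covariances must then add up to minus the total power, so negative dependence is built in. Because the coherence formula takes a magnitude, this dependence is reported as positive coherence.

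Two things are at stake in the primary endpoint. A real change in coherence between arms could appear as no change or as a change in the wrong direction. Amplitude and band power would also lose whatever activity the four sites share, and that loss depends on the coherence itself. The stated purpose does not justify this cost, because the article describes no source-localization analysis.

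**Working it through.** **Inputs.** From the article: four sensors, the average reference, and the coherence formula |Pxy| / (√Pxx · √Pyy). The article gives no coherence values and no figure for the effect of re-referencing, so there is no plan figure to reproduce. All coherence values below are assumptions, for in-phase signals of equal power (set to 1).

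**Formula.** Let S be the cross-spectral matrix at one frequency, m_i the mean of row i, and m the mean of all 16 entries. After subtracting the four-channel mean:

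R_ij = S_ij − m_i − m_j + m

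Coherence is then |R_ij| / √(R_ii R_jj).

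**Case 1: all six pairs share one coherence c.**
- m_i = m = (1 + 3c)/4.
- Power: R_ii = 1 − (1 + 3c)/4 = 0.75(1 − c). This is 0.75 at c = 0, 0.525 at c = 0.3, 0.375 at c = 0.5 and 0.15 at c = 0.8.
- Covariance: R_ij = c − (1 + 3c)/4 = −0.25(1 − c).
- Coherence: 0.25/0.75 = 1/3 for every c below 1, including c = 0. With five channels in the average it is 1/4.

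**Case 2: unequal coherences, all six raised by 0.20.** Values are listed as forehead–forehead / ear–ear / same-side / cross.

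Before, 0.60/0.50/0.55/0.45:
- Forehead row mean (1 + 0.60 + 0.55 + 0.45)/4 = 0.65. Ear row mean 0.625. Grand mean 0.6375.
- Forehead power 1 − 1.30 + 0.6375 = 0.3375. Ear power 1 − 1.25 + 0.6375 = 0.3875.
- Forehead covariance 0.60 − 1.30 + 0.6375 = −0.0625.
- Forehead coherence 0.0625/0.3375 = 0.185.

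After, 0.80/0.70/0.75/0.65:
- Row means 0.80 and 0.775. Grand mean 0.7875.
- Forehead power 0.1875. Forehead covariance 0.80 − 1.60 + 0.7875 = −0.0125.
- Forehead coherence 0.0125/0.1875 = 0.067.

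| Pair type | True | Re-referenced |
|---|---|---|
| Forehead–forehead | 0.60 → 0.80 | 0.185 → 0.067 |
| Ear–ear | 0.50 → 0.70 | 0.290 → 0.263 |
| Same-side | 0.55 → 0.75 | 0.242 → 0.178 |
| Cross | 0.45 → 0.65 | 0.518 → 0.652 |

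Three of the four pair types fall although every true value rose. The cross pairs move the right way.

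**Case 3: one pair changes.** With the other five pairs at 0.3, a true AF7–AF8 rise from 0.3 to 0.6 reads as a fall from 0.33 to 0.03. A rise from 0.6 to 0.9 reads as a rise from 0.03 to 0.67. The same true step can therefore read in either direction.

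**Check of the alternative.** For AF7–TP9 against AF8–TP10 at equal power, coherence is |ff + ee − 2·cross| / [2(1 − same-side)]. It is unchanged by subtracting any common signal.
- Independent channels: 0, as it should be.
- Case 2: 0.20/0.90 = 0.22 before and 0.20/0.50 = 0.40 after, in the true direction.
- Equal c on all pairs: 0 for every c below 1, so a change common to all sites is invisible.
- From 0.5/0.5/0.5/0.4 to 0.7 throughout: it falls from 0.20 to 0.00, so it too can fall when all coherences rise.
- Independent noise of 5-fold amplitude on one ear sensor, in the Case 2 starting state: it drops from 0.22 to 0.04.

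**The case against.** **Does the step reach coherence at all?** The article ties it to source localization and never says which reference coherence uses. This is fair, but the section describes one sequence, with coherence after re-referencing and no return to the recorded reference. A programmer following the text would compute coherence on re-referenced data.

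**A reader might infer that coherence is fixed near 1/3 whatever the true connectivity.** The documents and the arithmetic do not support this. The value 1/3 needs equal power and the same in-phase coherence on all six pairs. In Case 2 the values run from 0.07 to 0.65. Over 20,000 random sets of positive coherences (0 to 0.9, equal power), the 5–95% range was 0.05 to 0.83 and only 13% of values fell within 0.05 of 1/3. Those shares depend on the assumed distribution.

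**The recorded reference is not truth either.** Activity at a shared reference adds an equal in-phase component to every channel and can itself inflate coherence. The article's remark about a non-scalp reference points to this. The objection stands, and it is why coherence should move to bipolar derivations rather than stay on the recorded reference. Amplitude and power would still be relative to that reference.

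**A badly seated sensor.** A reader might infer a fixed several-fold contamination of the other three channels. The size depends on the baseline. For 5-fold-amplitude noise on one ear sensor at c = 0.3, power in the others rises 4.0-fold against re-referenced power but is about 2.1 times raw power. The article also provides a contact display, artifact rejection and ICA.

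**Weight.** Coherence is one of several parameters under an undivided endpoint in a pilot, and the abstract omits it. That limits the reach of the point. However, amplitude and power, which the abstract does list, pass through the same step.

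**Conclusion.** The step is wrong as written for these outcomes. Its stated purpose is not carried out in the article. Followed literally, it gives a coherence of 1/3 for four independent equal-power channels, lets a real rise appear as a fall, and reduces channel power to 0.75(1 − c) in the equal case. The constraint that the signals sum to zero, with the negative dependence it forces, is exact and needs no assumption about the data. The numerical sizes rest on assumed in-phase coherences and equal power, and on reading the order of the text as the order of processing. How far the trial's own results would shift cannot be derived from the documents. The defect is worth correcting before any EEG data are processed. It concerns the processing of the EEG parameters, not the trial design as a whole.

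**What to change.** 1. Remove the average-reference step, and the words that give source localization as its purpose, from the pipeline that feeds amplitude, power and coherence.
2. Compute coherence once per band, between the left derivation AF7–TP9 and the right derivation AF8–TP10.
3. State that AUXR is excluded from these analyses.
4. State that amplitude and power are reported relative to the recorded reference.

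**Cost.** A change to the processing script and a few sentences of text, with no new data. The downsides should be written into the plan:
- There is one left–right coherence value per band instead of six sensor pairs.
- The measure has no sensitivity to activity common to all four sites, and it can fall when all coherences rise.
- It remains sensitive to a badly seated sensor, so contact quality and artifact handling still matter.
- Amplitude and power keep any contribution from the recorded reference.

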### Study goal and objective

If an earlier, migraine is left untreated or undiagnosed, it is reported that around 2.5% of individuals with migraine are considered to have a chronic condition, defined as presenting with more than 15 headache days within a month. Subclassifications of the disease (migraine with and without aura and chronic migraine) occur clinically at various severity levels and coexist with numerous comorbidities. For this reason, several studies encourage a multidisciplinary and tailored treatment approach for these patients [26,27]. This preliminary randomized control trial aims to analyse the effectiveness of aerobic training among university students with migraine symptoms. The main objective is to determine the preliminary effect of aerobic training on migraine pain level, sleep quality, quality of life, and resting-state brain waves compared with EMG biofeedback training and placebo.

The alternative hypothesis of this study will be the aerobic training will be superior to EMG biofeedback training and placebo group in improving migraine pain level, sleep quality, quality of life, and resting-state brain waves. The null hypothesis will be the aerobic training is same as to EMG biofeedback training and placebo group in improving migraine pain level, sleep quality, quality of life, and resting-state brain waves. Although the Migraine Research Foundation listed three main types of non-drug treatments for migraine: lifestyle advice, therapies, and exercises. Some common aerobic exercises such as walking, jogging, a behavioral weight loss program, cycling, and a combination of cross-training, walking, jogging, and cycling are suggested to be beneficial to migraine patients but there remains no specific protocol established till now. Hence, this study will contribute to the research field by establishing an aerobic training protocol for patients with migraine symptoms.

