### Outcomes

The primary endpoint is resting-state EEG, and the secondary endpoints are sleep quality, quality of life, and migraine pain level. The Confounders will be the level of migraine pain (Russo et al., 2018), gender (Victor et al., 2010) (Kelman, 2006), and age (Echiverri et al., 2018), COVID-19 (Haghdoost et al., 2021).

The migraine pain level questionnaire that records the general health condition of the participants and the characteristics of migraine which including, frequency, severity, and duration will be included. Level of pain scored on a four-point numerical rating scale (0–3) equivalent to no, mild, moderate, and severe pain [36]: 0 no pain. 1 mild pain, does not interfere with usual activities 2 moderate pain, inhibits but does not wholly prevent usual activities 3 severe pain, prevents all activities. The other components are expressed as either decreased/ increased/ remains the same/ unable to recall.

Pittsburgh Sleep Index is a self-rated questionnaire that assesses sleep quality and disturbances over a 1-month interval. 19 individual items generate seven component scores: subjective sleep quality, sleep latency, duration, habitual sleep efficiency, sleep disturbances, use of sleeping medication, and daytime dysfunction. The sum of scores for these seven components yields one global score. The sleep component scores are summed to yield a total score ranging from 0 to 21, with the higher total score (referred to as global score) indicating worse sleep quality [37].

Migraine Specific Quality of life is a 14-item instrument that measures the impact of migraine across three essential aspects of a patient’s health-related quality of life over the past 4 weeks: role function-restrictive (RR), role function-preventive (RP), and emotional function (EF). Raw dimension scores are computed as a sum of item response and rescaled from a 0 to 100 scale. The higher the score better is the quality of life [38].

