#### Biofeedback training

Participants in this group will undergo an electromyography (EMG) biofeedback training for the trapezius and frontalis using a rose for relaxation 3 times per week for 6 weeks. Each session will be 30 minutes, with a 5-minute resting period between each muscle session. Fig 6 summarizes the biofeedback training protocol.

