**Fig 6 pone.0291534.g006:**
[figure not shown]
Protocol of biofeedback training. a- biofeedback training device, b- frontalis electrdode placement, c- training device display/feedback, d- trapezius electrode placement.

Neurotrac myoplus 4 pro instrument will be used for EMG biofeedback training. The rose game for relaxation provides an EMG biofeedback when the participant’s rose opens when relaxation is detected, and the aim is to relax completely and stay relaxed. 4 microvolt is the default value which can still be lowered one’s relaxation ability is achieved. During each training session, the electrodes will be placed on Frontalis and Trapezius muscle. The electrodes are connected to this machine that gives feedback to the participant via a visual signal, allowing them to decrease or increase muscle activity. During the training sessions, the patient will be made to sit in a comfortable chair with a straight back, feet flat on the floor (forming 90 –degrees with knees and with arm-rest and instructed to maintain erect sitting throughout [48].

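### Biofeedback trains the forehead muscle under the EEG sensors, and ICA on four average-referenced channels cannot reliably separate that muscle signal from brain signal or leave coherence interpretable

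*Protocol article*

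**What the plan says.** Outcomes names the endpoint: "The primary endpoint is resting-state EEG, and the secondary endpoints are sleep quality, quality of life, and migraine pain level". The same section describes the device: "The headset has four dry sensors (two mastoid and two forehead sensors"). Its channel list starts with TP9 and continues "AF7 (left forehead), AF8 (right forehead), TP10 (right ear), AUXR (right auxillay"), which makes five names for a headset said to have four sensors. Participants are asked to avoid clenching the teeth and frequent blinking; forehead tension is not mentioned.

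The section on biofeedback training states: "Participants in this group will undergo an electromyography (EMG) biofeedback training for the trapezius and frontalis using a rose for relaxation", three times a week for six weeks, and says of the exercise that "the aim is to relax completely and stay relaxed". Neither other arm is described as training the frontalis. The Background says that regular EMG biofeedback gives a durable fall in muscle tension.

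Study goal and objective gives this hypothesis: "the aerobic training will be superior to EMG biofeedback training and placebo group in improving migraine pain level, sleep quality, quality of life, and resting-state" (the last item being the EEG endpoint). One planned contrast on the primary endpoint therefore runs through the biofeedback arm.

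Analysis of EEG signals sets a 1 Hz high-pass filter, then an average reference, and then: "Artifact rejection and ICA will be used to remove artifacts such as muscle, eye blinks, or eye movements without removing the affected data portions". Five bands are analysed, including beta (13–30 Hz) and gamma (31–40 Hz), together with band ratios, power spectral density and coherence. Coherence is defined as the modulus of the cross-spectrum over the product of the square roots of the two auto-spectra, that is, unsquared.

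**The concern.** One arm's treatment acts directly on a source of artefact in the primary endpoint. If training works as the Background expects, forehead muscle activity at week 6 is lower in that arm. This change arises after randomisation, so randomisation does not balance it and baseline adjustment does not remove it. Blinding the assessor does not touch it either, because it is physical. The confounders listed under Outcomes are pain level, gender, age and COVID-19, not muscle activity.

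The protection then rests largely on ICA, with very few channels. At stake are two things. First, a beta or gamma difference between aerobic training and biofeedback could be read as a brain effect when part of it is forehead muscle. Second, coherence in any arm could reflect the referencing and the number of components removed rather than the brain.

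**Working it through.** The protocol gives no figure of its own on this point, so the check is a count, some algebra and labelled illustrations.

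**1. Number of components.** Inputs: 4 sensors (Outcomes); average reference, which costs one dimension (Analysis of EEG signals). Maximum components = 4 − 1 = 3. After removing k components the data have rank 3 − k: rank 2 for k = 1, rank 1 for k = 2. If AUXR carried a real signal, the maximum would be 5 − 1 = 4, only one more. The stated targets for removal are muscle, blinks and eye movements, and muscle may have separate left and right sources.

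**2. Average reference alone.** Let four independent sources have equal power P. Each re-referenced channel is y_i = x_i − (x_1 + x_2 + x_3 + x_4)/4.
- Auto-spectrum: P(1 − 1/4) = 3P/4.
- Cross-spectrum of two channels: −P/4.
- Protocol coherence: (1/4)/(3/4) = 1/3 ≈ 0.33. Squared, it is 1/9 ≈ 0.11.

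**3. Two components removed.** Rank 1 means y_i = a_i·s for a single signal s. The cross-spectrum is a_i·a_j·P_ss, and the protocol's ratio is |a_i·a_j|·P_ss / (|a_i|·|a_j|·P_ss) = 1 for every sensor pair and every frequency, whatever the brain does.

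**4. Simulation of steps 2 and 3.** Four independent 1/f sources, 256 Hz, 300 s, random component directions; mean 8–12 Hz coherence:

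| Processing | Protocol formula (unsquared) | Squared |
|---|---|---|
| Raw | 0.05 | 0.003–0.004 |
| Average reference | 0.34 | 0.11 |
| Plus one component removed | about 0.53 | about 0.36 |
| Plus two removed | 1.00 | 1.00 |

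True coherence is zero in every row.

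**5. Separation of muscle.** An illustrative simulation had left and right frontalis, left and right temporal muscle, blinks and five brain sources on four average-referenced channels, with all amplitudes assumed. Frontalis was spread over two of the three components (74% and 88% of their 31–40 Hz power). Removing both leaves rank 1. The percentages depend on the assumptions; the limit of three does not.

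**6. Power bias.** False fall in band power = (muscle share of residual power) × (fall in muscle power). The document gives neither input. Under an assumed share of 20–60% and an assumed fall of 20–40%, the range is 0.2 × 0.2 = 4% to 0.6 × 0.4 = 24%. This shows only how the two inputs combine; it is not an estimate for this trial.

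**7. Would epoch rejection alone cure it?** Twenty minutes gives 20 × 60 / 2 = 600 two-second epochs. Assume muscle supplies 50% of 31–40 Hz power and is 30% lower in biofeedback. The simulated power ratio between arms was 0.86 without rejection. It was 0.89 with a threshold keeping 90% of the high-muscle arm's epochs, and 0.94 with one keeping 50%, which kept 76% in the biofeedback arm. Rejection shrinks the difference but does not remove it, and it is itself uneven between arms.

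**The case against.** Several counter-arguments have force.

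- **Safeguards.** The protocol names artefact rejection as well as ICA, and gives an instruction on clenching and blinking. This stands in part: the sentence also says that affected portions are kept, so how much rejection is meant is unclear. Thresholds and component rules may sit in a fuller document. The montage, average reference, ICA and retention of data are stated here, and the point concerns those.
- **Can ICA remove muscle?** A reader might infer that it cannot do so at all on four channels. That is too strong: some reduction is possible, and what fails is reliable separation that leaves usable brain signal. Eyes-closed segments also carry fewer blinks.
- **Order of steps.** The average reference is tied to source localisation. If it came after ICA, there would be four components, and three removals, not two, would be needed to reach rank 1. The text lists it before ICA.
- **Carry-over.** It may be said that carry-over of relaxation to the resting recording is undocumented. The Background's own claim of a lasting fall in tension answers this in part, but gives no amount.
- **Net direction.** The aerobic arm does neck exercise with a band secured around the head, so muscle activity may change there too. The direction of the net difference is not established.
- **Pilot status.** The trial is a pilot of preliminary efficacy. That lowers the severity but does not make a muscle difference a brain effect.

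**Conclusion.** The concern holds in a limited form and should be fixed. Forehead muscle signal can differ by arm at week 6 because biofeedback targets that muscle, and three components cannot reliably isolate it. This rests on two assumptions that the document does not quantify: that muscle activity overlaps 13–40 Hz, and that training carries over to the rest recording.

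A reader might infer a biased primary endpoint of known size, or bias in every EEG comparison. The document supports neither. The size of the power bias cannot be derived from it. The bias concerns mainly beta and gamma, and ratios built on them, in contrasts with biofeedback; aerobic versus placebo is not affected by this route.

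The coherence problem is firmer and wider. It is algebra and applies in all arms: about 0.33 from average referencing alone for independent equal-power sources, and exactly 1 if two components are then removed.

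**What to change.** In Analysis of EEG signals:

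1. Rest the primary aerobic-versus-biofeedback EEG conclusion on bands below 13 Hz. Label beta, gamma, and ratios or coherence using them, exploratory for contrasts with biofeedback.
2. Report forehead 31–40 Hz power by arm and visit as a check on muscle artefact.
3. Do not compute coherence on average-referenced, component-subtracted four-channel data. Use the original reference, with contaminated epochs rejected by a fixed threshold applied blind to arm. Report epochs retained per arm, because rejection reduces a sustained difference in muscle tone without removing it.

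In Outcomes:

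4. Reconcile the four sensors described with the five channels listed, and say whether AUXR enters the analysis.

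Cost: no added recording. Some epochs are lost, blinks in the coherence analysis are handled by rejection instead of correction, and beta and gamma no longer support a primary claim against biofeedback. The first change narrows the primary claim, so it should be settled before week 6 data are examined by arm.
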